#### Housing outcomes

The association of Miracle Friends with housing outcomes will be evaluated using logistic regression with a random intercept, modeling the dichotomized outcome of exited homelessness (1 = individual responded “My own apartment or home” or “Someone else’s apartment or home,” 0 = otherwise) as a function of treatment (1 = Miracle Friends group members who participated in at least one phone buddy intervention, 0 = waitlist group), with the same covariates and random intercept.

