***Primary outcomes***	
Housing status	Housing status is measured using questions from the Los Angeles County Homeless Count demographic survey [51]. Participants are asked, “In the past 30 days, please indicate all places where you have slept for at least one night.” Response options include (1) My own apartment or home; (2) Someone else’s apartment or home; (3) In a shelter, emergency, temporary housing; (4) Hotel/motel provided by an agency; (5) Outside on the street, park, or beach; (6) Tent or makeshift shelter; (7) In a bus station, train station, airport; Abandoned building; (8) In a vehicle (car, van, RV, truck); (10) An institution, hospital, or facility. A follow-up question could include, “If you stayed in more than one place, where did you stay the most?” Participants are also asked up to three possible questions with “yes” or “no” as response options. These include: Do you currently have a case worker who can help you with housing assistance? Do you currently have a housing assistance voucher? Are you on a waitlist for housing assistance?
Loneliness	UCLA Loneliness Short Version is a validated instrument [52] that measures three dimensions of loneliness: relational connectedness, social connectedness, and self-perceived isolation. Participants are asked three questions: (1) How often do you feel that you lack companionship? (2) How often do you feel left out? (3) How often do you feel isolated from others? Response options include: Hardly ever; Some of the time; Often
Social support	The Oslo Social Support Scale is a 3-item self-report measure of the level of social support [53]. Participants are asked three questions with different response options. The first is: “How many people are so close to you that you can count on them if you have great personal problems?” with response options of: None; 1–2; 3–5; or 5 + . The second is: “How much interest and concern do people show in what you do?” with response options of: None; Little; Uncertain; Some, or A lot. The third is: “How easy is it to get practical help from neighbors if you should need it?” with response options of: Very difficult; Difficult; Possible; Easy; or Very easy

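### The coding rule for exited homelessness names no survey item and, applied to the select-all housing item, counts a single night in a home as an exit

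*Protocol article*

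**What the plan says.** Table 1 lists housing status among the primary outcomes. The core item reads "In the past 30 days, please indicate all places where you have slept for at least one night". Its options begin "1) My own apartment or home; (2) Someone else’s apartment or home; (3) In a shelter, emergency, temporary housing" and go on to unsheltered places such as "5) Outside on the street, park, or beach; (6) Tent or makeshift shelter". Several options can be ticked together. Table 1 then adds: "A follow-up question could include, “If you stayed in more than one place, where did you stay the most".

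The Housing outcomes section turns this into a binary variable. Exited homelessness is 1 if the "individual responded “My own apartment or home” or “Someone else’s apartment or home" option was given, and 0 otherwise. The section names no source item. It sets no minimum number of nights and does not say what happens when a home option is ticked together with a street, tent, vehicle or shelter option.

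The Statistical power section uses the same outcome at Quarter 5. It assumes 60% versus 10% exiting for Miracle Money against waitlist, and 25% versus 10% for Miracle Friends against waitlist, with at least 105 per arm. It claims power above 95% and above 60% respectively. (The text attaches the 25% to Miracle Money, but the sentence concerns Miracle Friends.)

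**The concern.** The only item with listed options has a one-night threshold, and the coding rule adds no condition of its own. Put together as written, they make one night in anyone's home during the past month enough for an exit, wherever the other 29 nights were spent. That is not what a reader would take exited homelessness to mean.

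The alternative is to score the place stayed most, which gives a different variable. Two analysts could each follow the text faithfully and report different results on a primary outcome, with the choice made after the data are in hand.

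If the any-night version is used and still-homeless people tick a home option equally often in each arm, recorded exit rates rise everywhere and the difference between arms shrinks. If they do so at different rates, the estimate is biased in a direction that cannot be known beforehand.

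**Working it through.** **Reading the two sections together.** Take a person with 29 nights in a tent and one night in a friend's home:

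- Select-all item scored: both places are ticked, a home option was given, so the code is 1.
- Follow-up item scored: the place stayed most is the tent, so the code is 0.

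The Housing outcomes section fits either reading. A person who stayed mostly in someone else's home is coded 1 under both.

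**The plan's own power figures.** Inputs from Statistical power: 105 per arm, threshold 0.05 (sidedness not stated; two-sided assumed), unadjusted comparison of two proportions.

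- Arcsine method, 25% versus 10%: h = 2·asin(√0.25) − 2·asin(√0.10) = 0.404. Then h·√(105/2) − 1.96 = 0.965, which gives power 83.3%.
- Pooled-variance method, 25% versus 10%: (0.15 − 1.96·√(2·0.175·0.825/105)) / √((0.1875 + 0.09)/105) = 0.918, which gives power 82.1%.
- 60% versus 10%: above 99.9% by both methods.

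Both stated lower bounds are therefore true; the 60% bound is loose.

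**Illustration of the any-night rule.** Let f be the share of people who have not exited but spent at least one night in a home. The documents do not give f; 5% to 30% is an assumed range. Treat 25%, 60% and 10% as true exit rates and take f as equal in both arms. The recorded rate is p + f(1 − p), so the recorded difference is the true difference times (1 − f).

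Miracle Friends versus waitlist, 105 per arm:

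| f | Recorded rates | Difference (points) | Power (pooled / arcsine) | Waitlist exits that are false |
|---|---|---|---|---|
| 0 | 25% vs 10% | 15 | 82% / 83% | 0% |
| 5% | 28.8% vs 14.5% | 14.25 | 71% / 72% | 31% |
| 10% | 32.5% vs 19% | 13.5 | 61% / 62% | 47% |
| 20% | 40% vs 28% | 12 | 45% / 45% | 64% |
| 30% | 47.5% vs 37% | 10.5 | 34% / 34% | 73% |

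The last column is 1 − 0.10 / recorded waitlist rate; at f = 10%, 1 − 0.10/0.19 = 47%.

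**Larger groups.** Results gives 169 matched in Miracle Friends only and 233 on the waitlist (the Abstract says 237, which changes power by less than one point). Before attrition, √(169·233/402) = 9.90 replaces √(105/2) = 7.25. Power by the arcsine method is then 87%, 71% and 56% at f = 10%, 20% and 30%.

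**Miracle Money versus waitlist.** The 50-point difference becomes 45, 40 and 35 points at f = 10%, 20% and 30%. Power stays above 99%.

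**The case against.** The strongest reply is that the rule does not say the select-all item is scored. A mutually exclusive 1/0 coding suits the follow-up on the place stayed most just as well, and coding of multiple responses often sits in an analysis plan that is not shown here. The first half stands: a reader might infer that the trial will definitely count one night as an exit, and the documents do not establish that. The second half does not remove the point, because the article itself states the 1/0 coding, and that coding as stated admits the one-night case. The follow-up is introduced only as something that could be asked.

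Three further inferences are tempting and not supported:

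- *That counting someone else's home is an error.* It is an openly stated definitional choice. Whether staying with others is still homelessness under the federal definition used for entry cannot be checked, because its content is not in the documents. For the same reason, it cannot be shown that eligible people would already score as exited at baseline.
- *That the rule will manufacture a benefit.* With no true effect and a 10% exit rate, f of 20% against 10% gives 28% versus 19%, a 9-point false gain. Reversing the two values gives a 9-point false loss. Both splits are invented. The treated group in the Housing outcomes model is Miracle Friends members, who as a group are not offered cash, so a story about money buying nights indoors does not fit that contrast.
- *That power is lost by a known amount.* The range for f is assumed. If 25% and 10% already refer to the coded outcome, adding f counts it twice. At f = 10%, power at 105 per arm still meets the stated bound of 60%, and the groups reported in Results are larger.

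**Conclusion.** The point holds as a defect in how a primary outcome is fixed. The rule is not tied to a survey item, is silent on mixed answers, and when applied to the only item with listed options scores one night in a home as an exit. It should be settled before Quarter 5 housing data are analysed.

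The existence of the ambiguity rests on the text alone. Its size does not: every figure for dilution or power depends on an assumed f, on f being equal across arms, and on the planning rates being true exit rates. Under those assumptions the Miracle Friends comparison is the vulnerable one. For Miracle Money the risk is an understated effect and not a missed one.

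**What to change.** In the Housing outcomes section:

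1. State that the outcome is scored from the place stayed most in the past 30 days. This is the follow-up answer where several places were ticked, and the single place where only one was.
2. State how respondents who ticked several places but have no follow-up answer are coded.
3. Report own home and someone else's home as separate categories beside the combined outcome.
4. Pre-specify two sensitivity analyses: own home only, and the any-night rule.

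Do not make the absence of any night elsewhere part of the primary rule. A person who moved from a shelter into an apartment three weeks before the survey would then be scored as not exited.

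The cost is a few sentences and mostly recoding of survey answers. The recorded exit rate may be lower than under the any-night rule. Because Table 1 describes the follow-up only as possible, it may be missing for some multi-place respondents, and the number affected should be reported by arm.

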To better understand the impact of the Miracle Friends intervention and how adding basic income influences outcomes, the Miracle Messages nonprofit and the University of Southern California Suzanne Dworak-Peck School of Social Work established a community–academic partnership in 2022 to design and conduct a randomized controlled trial of these interventions. Through private philanthropy, funding was secured to provide basic income to as many of 105 individuals for 1 year. The study takes place in the Los Angeles and San Francisco Bay areas of California, which have high rates of homelessness. California accounts for 30% of all people in the USA experiencing homelessness, including half (*n* = 115,491) of all unsheltered people, many of whom reside in the Los Angeles and San Francisco Bay areas [39]. In these urban regions and nationally, African Americans are overrepresented in the homeless population. Nationally, African Americans comprise 40% of the homeless population while representing only 13% of the general population [39]. This is an important factor to consider for this study, because although Whites are more likely to become homeless due to individual risk factors such as health impairments or disabilities, research suggests that African Americans are more likely to become homeless due to lack of income and social capital [43], both of which are target outcomes for the Miracle Money intervention [44]. However, it is unclear whether increased income and social support can overcome other forms of discrimination experienced by African Americans that may be required to exit homelessness [45].

The overarching research questions that this study seeks to answer are: (1) Is the Miracle Friends intervention associated with reduced social isolation and increased social support? (2) Is the Miracle Friends intervention associated with improved housing outcomes? (3) Does the addition of basic income through the Miracle Money intervention improve these outcomes of interest? (4) Are there differences in outcomes based on race?

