## Methods

### Design overview

Miracle Messages, the nonprofit that delivers the Miracle Friends and Miracle Money interventions, is headquartered in the San Francisco Bay Area but expanded to have staff members in Los Angeles for this study. Through partnerships with homeless service agencies or direct street outreach, Miracle Messages staff members engaged unhoused individuals to explain the Miracle Friends intervention, which requires having a phone, and signed up anyone who expressed interest in a phone buddy. Those who signed up also learned about a study to evaluate the Miracle Friends intervention, and those who expressed interest were referred to a study team affiliated with the University of Southern California. For those who agreed and provided written informed consent to participate in the study, a random number generator was used to determine sequentially whether a study participant would be offered the Miracle Friends intervention or put on a waitlist. Participants were told that they had a two-thirds chance to be offered Miracle Friends but were not told that approximately half of those offered Miracle Friends would be assigned to a third arm of the study that could receive basic income. For this group, receiving basic income through Miracle Money was contingent on participating in Miracle Friends. Figure 1 depicts how participants were randomized using a parallel-group trial design to one of three groups with a 1:1:1 allocation ratio: (a) those offered Miracle Friends only; (b) those who would be offered Miracle Money if they participated in Miracle Friends; and (c) those on a waitlist for Miracle Friends. Recruitment continued until at least 100 people began receiving Miracle Money.

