### Quantitative data analysis

#### Social isolation outcomes

To evaluate the efficacy of the Miracle Friends intervention on social support, psychological distress, and loneliness, we will use responses to the Oslo Support Scale [53], Kessler Psychological Distress Scale [55], and UCLA Loneliness Scale [52], respectively, at the final survey (Quarter 5). Each measure will first be summed to develop a total score, then dichotomized based on cutoffs for each measure based in the literature—i.e., poor social support will be coded as 1 if the Oslo Support Scale sum score is less than 9 (indicative of poor social support) and 0 otherwise; psychological distress will be coded as 1 if the Kessler Psychological Distress Scale sum score is greater than 25 (indicative of high psychological distress) and 0 otherwise; and loneliness will be coded as 1 if the UCLA Loneliness Scale sum score is greater than or equal to 6 (indicative of high loneliness) and 0 otherwise. Each dichotomized score will be modeled as a function of treatment group (1 = Miracle Friends or Miracle Money group members who participated in at least one phone buddy intervention, 0 = waitlist group); covariates including demographic characteristics, physical and mental health, and substance use; and a random intercept for city in random intercept logistic regression models.

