#### Statistical power

To reach a target goal of 105 participants receiving basic income through Miracle Money, recruitment efforts have yielded more than 200 individuals in each treatment group. Assuming that each arm will have at least 105 participants, our study can detect the hypothesized 50% difference in proportion of people exiting homelessness at Quarter 5 between the Miracle Money and waitlist group (assuming 60% of the Miracle Money group exits homelessness and 10% of the waitlist group exits homelessness) using a *p*-value threshold of 0.05 with power exceeding 95%. When comparing the Miracle Friends group to the waitlist group, our study can detect the hypothesized 15% difference in proportion of people exiting homelessness at Quarter 5 between the Miracle Friends and waitlist group (assuming 25% of the Miracle Money group exits homelessness and 10% of the waitlist group exits homelessness) using a *p*-value threshold of 0.05 with power exceeding 60%. Differences in proportions of the social isolation outcomes will be detected at powers identical to the housing outcome, assuming identical differences in proportions and *p*-values. Regarding the effect modification of treatment by race in exiting homelessness, our study will be able to detect a difference in proportion of groups exiting homelessness of 35% with power exceeding 20%. Main effect calculations were done on unadjusted models using the WebPower R package, and the effect modification power calculations were performed via simulation.

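### No stated model isolates Miracle Money: it is pooled with Miracle Friends for the social outcomes and omitted or pooled for housing, although research question 3 and the power section call for it

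*Protocol article*

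**What the plan says.** Participants are allocated "to one of three groups with a 1:1:1 allocation ratio" (Design overview): Miracle Friends only, Miracle Money conditional on taking part in Friends, and waitlist. The abstract's aim is to test each of the two interventions against the waitlist. Among the research questions at the end of the Background, the third is: "Does the addition of basic income through the Miracle Money intervention improve these outcomes of interest".

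The analysis section gives explicit codings.

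- **Social isolation outcomes** (social support, psychological distress, loneliness): one binary term, "1 = Miracle Friends or Miracle Money group members who participated in at least one phone buddy intervention, 0 = waitlist group". Its stated purpose is to evaluate the efficacy of Miracle Friends.
- **Housing outcomes**: "The association of Miracle Friends with housing outcomes will be evaluated using logistic regression with a random intercept", with treatment coded 1 for "Miracle Friends group members who participated in at least one phone buddy intervention" and 0 for the waitlist.
- **Differences by race**: the same models with a race-by-treatment interaction added.

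The Statistical power section gives its leading power figure for the difference in people "exiting homelessness at Quarter 5 between the Miracle Money and waitlist group", assuming 60% versus 10%. It then gives a figure for Friends versus waitlist.

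**The concern.** Research question 3 needs a Money versus Friends contrast, and the first power statement needs a Money versus waitlist contrast. Neither can be read from a coefficient in the stated models.

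Two consequences follow if the text is applied literally. First, the analyses contain no estimate of what $750 a month adds, which is one of four research questions. Second, the social isolation models answer question 1 with a mixture. Some of those coded as treated also received cash, so any benefit of income on loneliness, distress or support would be reported as a benefit of phone buddies. If the missing contrasts are chosen after outcome data are seen, the Money result will also be hard to present as confirmatory.

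**Working it through.** **1. Contrasts needed against contrasts stated**

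| Contrast | Called for by | In a stated model? |
|---|---|---|
| Friends vs waitlist, social outcomes | Question 1 | Only mixed with Money |
| Friends vs waitlist, housing | Question 2, power section | Yes, if the housing code means the Friends-only arm |
| Money vs Friends, all outcomes | Question 3 | No |
| Money vs waitlist, housing | Abstract aim, power section | No |
| Money vs waitlist, social outcomes | Abstract aim; the power section carries its figures over to these outcomes | No |

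The social isolation section names the Friends and Money groups separately, so the housing code most naturally means Friends only. On the wider reading Money is pooled there as well. Question 3 has no estimate on either reading.

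**2. The protocol's power figures** (105 per arm, two-sided 0.05 assumed, pooled z-test for two proportions)

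- Money vs waitlist, 60% vs 10%: power above 99.99%. The stated figure, exceeding 95%, is consistent with this, but no stated model makes the comparison.
- Friends vs waitlist, 25% vs 10%: power about 82%. The stated figure, exceeding 60%, is true as a lower bound. The text attaches the 25% to Money; I read it as the Friends rate because the sentence concerns Friends versus waitlist.

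**3. Illustration of the mixing in the pooled term**

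Inputs: 360 matched across the two intervention arms (169 Friends, 191 Money) and 103 paid (Results); differences from waitlist of 60 − 10 = 50 points for Money and 25 − 10 = 15 points for Friends (Statistical power). The number who count as having participated is not given, so I take matched as participated. I also apply housing differences to social outcomes, which the power section does only conditionally.

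- Share paid: 103/360 = 29%.
- Matched but unpaid: 360 − 103 = 257, assigned the Friends difference.
- Pooled difference: (103 × 50 + 257 × 15)/360 = 9005/360 = 25 points, against 15 for Friends.
- Part due to cash: the 50 points are Friends plus income, so the increment is 50 − 15 = 35 points, and 103 × 35/360 = 3605/360 = 10 points.

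If only the 103 verified Money participants and all 169 matched Friends members count, the pooled difference is (103 × 50 + 169 × 15)/272 = 7685/272 = 28 points. With equal arms and every Money member at 60%, it is (50 + 15)/2 = 32.5 points. The size depends on the assumption. The direction does not, as long as cash has a benefit.

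**4. Would the missing contrast be feasible?**

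Money vs Friends at 60% vs 25%, 105 per arm: power 99.96%.

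As randomised (267 vs 256), with complete follow-up and two-sided 0.05, the result depends on how unpaid and unmatched people fare:

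- Paid 60%, everyone else in both arms 25%: Money arm (103 × 0.60 + 164 × 0.25)/267 = 38.5% vs 25%; power about 91%.
- Paid 60%, matched unpaid 25%, unmatched 10%: Money (103 × 0.60 + 88 × 0.25 + 76 × 0.10)/267 = 34.2%, Friends (169 × 0.25 + 87 × 0.10)/256 = 19.9%; power about 96%.
- Paid 60%, all others in the Money arm 10%, Friends arm as in the previous line: Money (103 × 0.60 + 164 × 0.10)/267 = 29.3% vs 19.9%; power about 70%.

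So the contrast is worth specifying. These figures would fall with loss to follow-up or a stricter significance threshold.

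**The case against.** The strongest reply is that a Money comparison plainly is intended. The abstract promises a test of each intervention, and the power section fixes an outcome, a time point and a significance threshold for Money versus waitlist. This is also a condensed article, and a full protocol or analysis plan may list the contrasts. The first part stands, and it shows that the document contradicts itself. It does not supply question 3, because Money versus waitlist gives Friends and income together, not what income adds. The second part would carry weight if the article were silent. It is not: it states exact 0/1 codings, and those codings exclude the contrast.

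A second reply is that the members named in the housing code could include the Money arm, whose members are also offered Friends. That is possible, so one cannot say with certainty that the Money arm is absent from the housing model. Money would then be pooled, and question 3 would still have no estimate.

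Three stronger readings are tempting and are not supported:

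- That the trial cannot answer question 3. Three-arm randomisation with the same survey schedule in every arm can answer it; the gap is in the stated models.
- That 267 of 523 people in the pooled code belong to the Money arm. Those are the numbers randomised, while the code admits only people who took part in the phone-buddy programme, and that number is not given.
- That the pooled model would show about 14 points (103 × 50/360) even if Friends did nothing. This credits the whole Money-versus-waitlist difference to cash. With the protocol's 15 points for Friends, the cash increment is 35 and its contribution is about 10.

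**Conclusion.** The point holds for the analyses as written. The Money versus Friends contrast is in neither the models nor the power section, and Money versus waitlist is powered but not modelled. The effect labelled as Miracle Friends on the three social isolation outcomes mixes two interventions.

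The textual finding needs no numerical assumption. The size of the mixing does. About 25 points against 15, with about 10 due to cash, is an illustration that takes matched as participated, reads the mislabelled 25% as the Friends rate and borrows housing differences for social outcomes. This should be corrected before outcomes are analysed, because the defect lies in the stated codings and the data already collected can support the right contrasts.

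**What to change.** In every model (housing, loneliness, social support, distress), replace the binary treatment code with a three-level arm factor, and pre-specify:

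1. Friends-only versus waitlist (questions 1 and 2);
2. Money versus Friends-only (question 3);
3. Money versus waitlist (the combined effect, and the comparison already powered).

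Carry the same factor into the race interaction models. Keep the pooled code, if wanted, only as a secondary contrast for any offer of a phone buddy. Correct the group label on the 25% rate in the power section and add a power statement for Money versus Friends.

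The cost is wording and a little more analysis, with no new data. The Friends versus waitlist contrast for social outcomes loses the Money participants and so some precision; that is the price of estimating the named intervention. Three contrasts across several outcomes also need a stated testing order or multiplicity rule. Whether treated status should rest on participation or on assignment is a separate matter that the three-level factor does not settle, and the text should state which is used.

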### Interventions

#### Miracle friends

Miracle Messages program staff members have recruited volunteers who want to serve as a phone buddy and unhoused individuals who expressed an interest in being matched with a phone buddy. Recruitment of volunteers has occurred primarily through people who learned about the program through media coverage, word of mouth, social media, or internet searches about helping PEH, with most volunteers signing up on the Miracle Messages website. Volunteers are required to complete an application listing any preferences for a friend (e.g., gender, language, shared interests, text or calls preferred) and attend a 30-min training call offered once a week synchronously. A recording of the training call is available as needed to those with significant scheduling conflicts. Volunteers receive a program handbook that outlines expectations for logging into an online platform to record any contact or attempted contact with an unhoused friend. After completing a waiver of liability, volunteers receive a phone number through Dialpad or similar service (which allows the volunteers to avoid divulging their personal phone numbers if they wish) and are subsequently matched with an unhoused friend, usually in a few weeks. Weekly support calls are offered to all volunteers, in addition to one-on-one support provided upon request based on completing the contact logs. Currently, there are approximately 300 Miracle Friend volunteers.

Recruitment of unhoused individuals has happened primarily through (a) site visits at local partner sites, including shelters, transitional housing facilities (e.g., tiny homes), converted hotels or motels for unhoused individuals, etc.; (b) referrals from caseworkers and social workers at these partner sites; and (c) limited direct outreach on the streets in and around partner sites or at events designed to address the needs of PEH (e.g., food pantries, homeless connect events). Miracle Friends program staff members explain the intervention and sign up anyone who expresses an interest in a phone buddy. Like with the volunteers, unhoused participants are also asked to complete an application listing any preferences for a friend (e.g., gender, language, shared interests, text or calls preferred).

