### Quantitative data collection procedures

Upon enrollment in the study and regardless of group assignment, the participants complete a baseline survey that takes approximately 45 min and includes questions about demographic characteristics, homelessness history, physical and mental health status, health service utilization, employment, substance use, socioeconomic status, and income. Participants are also asked to provide an email address and collateral contact information for one or more people to ensure that the study team can reconnect with them when it is time to complete a shorter survey five more times, one every 3 months (i.e., quarterly) until 15 months. The quarterly survey asks about similar topics and takes approximately 25 min. Surveys can be completed in person or over the phone, with responses recorded by a surveyor directly into the REDCap data management platform [49, 50] that is also used to support data visualization to monitor data quality and study retention. Upon request, participants also receive a link to self-administer the survey in English or Spanish. Table 1 describes all study measures.

**Table 1 Tab1:** Study measures and scales

Measure	Description

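### The housing model names no baseline housing covariate: this mainly costs precision in groups as randomised, and leaves housing position unadjusted when phone-buddy participants are compared with the whole waitlist

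*Protocol article*

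**What the plan says.** The Social isolation outcomes section gives the adjustment set as "covariates including demographic characteristics, physical and mental health, and substance use", plus a random intercept for city. The Housing outcomes section carries that set over "with the same covariates and random intercept" and adds nothing specific to housing. Its treated group is the Miracle Friends members who took part in at least one phone-buddy contact; its comparison group is the waitlist.

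Table 1 lists housing status as a primary outcome. Participants are asked about the past 30 days: "please indicate all places where you have slept for at least one night". The same measure asks "Do you currently have a case worker who can help you with housing assistance? Do you currently have a housing assistance voucher" and "Are you on a waitlist for housing assistance". None of the yes/no items appears in any analysis the article describes.

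On timing, the data collection section says: "Upon enrollment in the study and regardless of group assignment, the participants complete a baseline survey". It adds that the quarterly surveys cover similar topics. Homeless history is listed among the baseline-only items.

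On the spread of starting points, recruitment ran through "site visits at local partner sites, including shelters, transitional housing facilities (e.g., tiny homes), converted hotels or motels for unhoused individuals", caseworker referrals and limited street outreach.

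**The concern.** Everyone is homeless at entry, so the baseline value of the dichotomised outcome should vary little. Distance from that outcome can still vary a good deal. A voucher holder in a converted hotel and a person sleeping outside with no voucher plausibly have different chances of being in an apartment 15 months later, whatever the intervention does. The named covariates suit loneliness and social support; for a housing endpoint they leave out what is probably the most direct predictor.

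Two things are at stake. If groups are compared as randomised, an available source of precision on a primary outcome goes unused. In the comparison as planned, people enter the treated group by taking part after randomisation. If taking part goes with housing position, the groups differ on it systematically, and no named covariate measures it directly.

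**Working it through.** **1. The plan's own power figure.** The Statistical power section gives 105 per arm, 25% v 10% exits, threshold 0.05 and power exceeding 60%. With the two-sided pooled formula:

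- mean proportion 0.175; null SE = sqrt(2 × 0.175 × 0.825 / 105) = 0.0524
- alternative SE = sqrt((0.25 × 0.75 + 0.10 × 0.90) / 105) = 0.0514
- power = Φ((0.15 − 1.96 × 0.0524) / 0.0514) = Φ(0.92) = 82.1%

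The arcsine form gives 83.3% and a continuity correction 76.8%. The stated figure is true as a lower bound, but it is not what these inputs produce. The present point does not depend on it; about 82% is the unadjusted starting value below.

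**2. Precision in groups as randomised.** The documents give neither the prevalence nor the prognostic strength of any baseline housing item, so both are assumed. Trials were simulated with 105 per arm and marginal exit rates of 10% and 25%. A logistic Wald test was run without and with one binary baseline marker that randomisation balances in expectation.

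| Marker odds ratio (assumed) | 20% prevalence, 1,500 trials | 25% prevalence, 4,000 trials |
|---|---|---|
| 3 | 82.8% to 83.3% | 82.7% to 84.0% |
| 6 | 82.0% to 85.8% | 82.8% to 86.3% |
| 10 | 81.9% to 88.5% | 82.8% to 89.2% |

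Each figure from 1,500 trials has a simulation SE of about 1 point (sqrt(0.82 × 0.18 / 1500) = 0.0099). The gain is slight at an odds ratio of 3 and useful at 6 to 10.

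**3. Chance imbalance.** No stratification is stated. For a trait held by 25% (assumed), the 95% range is 1.96 × sqrt(0.25 × 0.75 × (1/n1 + 1/n2)):

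- 256 v 237: ±7.7 points
- 105 v 105: ±11.7 points

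To put this on the outcome scale, assume exit rates of 30% for people near housing and 5% for others, a gap of 25 points. Those extremes then move the risk difference by 0.077 × 25 = 1.9 points and 0.117 × 25 = 2.9 points. The hypothesised difference is 15 points.

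**4. The comparison as planned.** The Results section reports 169 of 256 Miracle Friends participants matched so far, a guide to how many could be coded as treated. The waitlist is taken as 233, as in that section. The abstract says 237, and only 237 brings the three arms to 760 (256 + 267 + 237), but the difference is immaterial here. Assume no true effect, the same 30% and 5% exit rates, and 20% of the waitlist near housing, so the waitlist exit rate is 0.2 × 30% + 0.8 × 5% = 10%.

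| Participants near housing | Spurious risk difference | Odds ratio | Chance of a falsely significant benefit (nominal 2.5%) |
|---|---|---|---|
| 25% | 0.05 × 25 = 1.25, about 1.3 points | 1.14 | about 6% |
| 30% | 0.10 × 25 = 2.5 points | 1.29 | about 12% |
| 40% | 0.20 × 25 = 5.0 points | 1.59 | about 33% |

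These are unadjusted comparisons. The named covariates and the city intercept may absorb part of the difference, to the extent that they track housing position.

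**5. Room for extra covariates.** At 105 per arm with 10% and 25% exits, expected events are 105 × 0.35, or about 37. Adding every housing item (a four-level place variable, three yes/no items and length of homelessness) costs 3 + 3 + 1 = 7 parameters on top of the existing covariates. The simulations added one, so they say nothing about a model of that size.

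**The case against.** The strongest reply is that the article does not exclude these items. The covariates are introduced by the word *including*, the article condenses a fuller plan that is not shown, and an itemised list normally sits in that plan. Homeless history shares a block with the demographic items in Table 1 and may already be covered. This stands against the statement that the model uses no baseline housing value; the documents support only that it names none. It does not dispose of the point, because the Housing outcomes section does more than stay silent: it ties the housing model to a list drawn up for the social outcomes.

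A reader might also infer that chance imbalance would bias the result. It would not. In groups as randomised, the error rate and the interval already allow for chance imbalance, and the shifts in step 3 are small beside 15 points.

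It is also fair to say that the more serious problem in step 4 is the choice of comparison groups, and that covariates cannot cure it. That stands. Adjustment would reduce only the part of the selection that the added items capture.

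Finally, baseline collection of each item is a sound inference but is not stated item by item. Table 1 speaks of up to three possible questions, and of a stayed-most follow-up that could be asked, so some values may be missing by design.

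**Conclusion.** The point holds in a limited form. The named covariates for a primary housing outcome contain no measure of baseline housing position, although the primary measure itself records it.

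In groups as randomised, the loss is precision: about 1 to 7 points of power at 105 per arm, on assumed odds ratios of 3 to 10 and prevalence of 20% to 25%. In the planned comparison of participants with the whole waitlist, differences in housing position can be systematic. On the assumed exit rates, a 10- to 20-point excess of people near housing would produce a spurious difference of 2.5 to 5.0 points. The direction and size of any such selection are unknown, and the documents do not show that it occurred.

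The change is worth making because it is cheap and the items very probably exist. It is an improvement to the model; the text does not contradict itself here.

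**What to change.** In the Housing outcomes section, replace the cross-reference to the social-outcome covariates with that list plus two baseline items:

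- place stayed most in the past 30 days (unsheltered v sheltered/other)
- housing voucher held (yes/no)

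First confirm that both were collected at baseline, and from whom. State how missing baseline values will be handled, and fix the list before Quarter 5 outcomes are analysed. Add caseworker, housing-waitlist status or length of homelessness only if the number of events supports them.

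The adjusted model should accompany a comparison of groups as randomised and not stand in for one.

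The cost is a change of wording, a few extra parameters and possibly some missing baseline values. No new data collection is needed if the items were asked at baseline.
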